### Research questions:

1. Is guided iTFCBT more efficacious than an active control condition (therapist-supported internet-delivered psychoeducation and support) in regard to reduction of blinded assessor rated PTSD symptom severity 1-month post-treatment?
2. Is guided iTFCBT more cost-effective than an active control condition (therapist-supported internet-delivered psychoeducation and support) in regard to reduction of blinded assessor rated PTSD symptom severity 1-month post-treatment?

3. Are the therapeutic gains of iTF-CBT maintained at long term follow up (6 and 12 months after treatment)?
4. How do children, parents and therapists perceive iTF-CBT?

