## DESCRIPTION OF THE STUDY

This study is a single-blind, parallel-group superiority trial with an internal pilot. Study participants will be randomly assigned to 12 weeks of either iTF-CT or therapist-supported internet-delivered psychoeducation on a 1:1 ratio without restriction. To prevent potential selection bias related to the randomization procedure, we will use an external party, the Karolinska Trial Alliance (KTA, [www.karolinskatrialliance.se](http://www.karolinskatrialliance.se)) for that. Allocation concealment will be ensured through randomization after the decision to include each participant has been made. Evaluation includes efficacy, cost-effectiveness, and long-term effects. Outcome measures will be evaluated at baseline, post-treatment, 1-months (primary endpoint), and 6- and 12-months follow-up by assessors blinded to treatment allocation. To ensure blinding integrity, participants and their guardians will receive explicit instructions not to disclose which treatment they have received. After completing the assessment, the blind raters guess the participant's group allocation. If participants inadvertently disclose the treatment allocation during the assessment, another blind assessor will re-assess the diagnosis based on recordings of the clinical interviews. Participants will be recruited nationally through self- or clinician referral. Self-referral will be made available through a dedicated secure website.

The first 20 included participants will not be randomized but will be part of an internal pilot. They will be asked to participate in process evaluation interviews after treatment completion. Interviews will also be conducted with therapists and clinicians recruiting to the study and providing treatment. The aim of this is to see that the recruitment and treatment procedures are feasible and acceptable and that retention to the trial are sufficient to allow the trial to progress.

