## SAMPLE SIZE

## OUTCOME MEASURES

The power analysis for the RCT is based on the gold-standard interview CAPS-5 where a clinically significant difference in treatment effects is 10 points, which is the between groups difference we aim to detect. With a standard deviation of the CAPS-5 to be 20, this represents a standardized mean difference in terms of Cohens  $d$  of 0.5 and to use it conservatively we used Cohens  $d$  0.4 in our calculations. The estimated number needed is then  $N=240$  (moderate between-group effect size against active control condition at 1-month post-treatment; 95% power, 10% data attrition rate, and an  $\alpha$  level of 0.04). All analysis will be conducted according to the intent to treat principle and we will follow the CONSORT guidelines in reporting and analyzing the data.

The primary hypothesis (clinician-rated CAPS-5-CA) will be evaluated using a linear mixed-effects model with fixed effects of time and group, their interaction, as well as random intercept and slope. Treatment response will be defined as at least 6 points improvement on the CAPS-5 between baseline and participants' last available measurement between baseline and 12-month follow-up (adapted from Schnurr & Lunney, 2016). Secondary self-rated outcomes will be estimated using linear mixed-effects models with repeated measurements and fixed effects of time and group, their interaction, as well as a random intercept and slope.

We will follow the Consolidated Health Economic Evaluation Reporting Standards (CHEERS) guidelines to report the health economic evaluation and look at both direct costs (e.g., therapist time per patient) and other societal costs (e.g., absence from school, caregivers' absence from work). Cost differences between iTF-CBT and the active control condition will be calculated, as well as the incremental cost-effectiveness ratio (ICER). The ICER is a global estimate of cost-effectiveness and represents the additional cost that is associated with the additional clinical effect in one intervention compared with another. Intra-Class Correlations will be used to calculate Interrater agreement on the CAPS-5-CA.

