## 1-MONTH FOLLOW UP

The same self-rated assessment questionnaires as at baseline will be used with the addition of the CAPS-5-CA interview. Qualitative interviews will also be conducted and scheduled separately. The assessment will include the need for further psychiatric care.

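### Treatment response is scored at each participant's last available CAPS-5 visit up to 12 months, so the response rate has no fixed time point and can differ between arms through drop-out timing alone

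*Protocol*

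**What the plan says.** The definition stands in the Protocol, in the paragraphs under SAMPLE SIZE / OUTCOME MEASURES: response is "at least 6 points improvement on the CAPS-5 between baseline and participants' last available measurement between baseline and 12-month follow-up". It is described as adapted from a cited source.

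Three other parts of the Protocol bear on it:

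- ASSESSMENT POINTS schedules the CAPS-5-CA at baseline, 1 month after treatment, 6 months and 12 months. It names the 1-month visit as the primary endpoint and the later two as secondary.
- The first research question compares the arms "in regard to reduction of blinded assessor rated PTSD symptom severity 1-month post-treatment".
- The primary hypothesis is tested with a linear mixed model on the CAPS-5-CA score (time, group, their interaction, random intercept and slope). That model does not use the response definition.

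**The concern.** A responder rate is read as the share of each arm that had improved by a stated time. Here the time is set by each participant's own follow-up. The 1-month score, which carries the trial's main question, is ignored for anyone seen again at 6 or 12 months and kept for anyone who was not.

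Two things are at stake. First, the rate cannot be set beside the primary result, because the two refer to different times. Second, if response changes over follow-up and one arm loses people earlier than the other, the rule produces a difference between arms where none exists at any visit. The direction depends on whether response rises or falls after 1 month, so the rule is not safely conservative.

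**Working it through.** **No plan figure to reproduce.** The Protocol states no expected response rate and no calculation for response. All rates below are assumptions chosen to show the mechanism.

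**Which visit counts.** From the schedule in ASSESSMENT POINTS and the definition:

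| Last CAPS-5 obtained | Visit used for response |
|---|---|
| 12 months | 12 months |
| 6 months | 6 months |
| 1 month | 1 month |
| Baseline only | Baseline, read literally: zero change, non-response |

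**Formula.** Let *b*, *d1* and *d6* be the shares of an arm last seen at baseline, 1 month and 6 months, and *p1*, *p6*, *p12* the true response at each visit. The reported rate is

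R = b × 0 + d1 × p1 + d6 × p6 + (1 − b − d1 − d6) × p12.

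To isolate the effect of timing, set *b* = *d6* = 0, give both arms the same true response at each visit, and assume that those who leave respond like those who stay. Write *d* for *d1*. Then

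R = d × p1 + (1 − d) × p12,

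and the difference (iTF-CBT, T, minus control, C) is

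(dT − dC) × (p1 − p12).

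The true difference is zero at every visit, so whatever this gives is artefact.

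**Main example.** p1 = 40%, p12 = 60%, dT = 30%, dC = 10%:

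- iTF-CBT: 0.30 × 0.40 + 0.70 × 0.60 = 0.12 + 0.42 = 54%
- Control: 0.10 × 0.40 + 0.90 × 0.60 = 0.04 + 0.54 = 58%
- Difference: 0.20 × (−0.20) = −4 points

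**Range.**

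| p1 → p12 (both arms) | Drop-out after 1 month, iTF-CBT v control | Reported response, iTF-CBT v control | Artefact |
|---|---|---|---|
| 40% → 60% | 10% v 10% | 58% v 58% | 0 |
| 40% → 60% | 30% v 10% | 54% v 58% | −4 points |
| 40% → 60% | 25% v 5% | 55% v 59% | −4 points |
| 60% → 40% | 30% v 10% | 46% v 42% | +4 points |
| 30% → 60% | 30% v 10% | 51% v 57% | −6 points |

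Response scored at one fixed visit with complete data has an artefact of 0 in every row.

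**Link to the plan's attrition.** The sample-size paragraph assumes "95% power, 10% data attrition rate" for the 1-month comparison. It does not divide the 10% by arm and says nothing of losses between 1 and 12 months, so 30% v 10% is an assumption. If overall later loss were also 10%, the widest split between equal arms would be 20% v 0%. That is again a gap of 20 percentage points, and at 40% → 60% it gives 56% v 60%, the same −4 points. A more even split gives less.

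**The case against.** **The measure is peripheral.** The primary test is the mixed model. PRIMARY MEASURES does not name treatment response among the primary or secondary outcomes; it lists clinician-rated symptom improvement, but does not tie this to the definition. No between-arm test of response is stated. This stands, and it limits the weight of the point. It does not remove it, since a defined response rate in a two-arm trial will be reported by arm.

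**Details belong in the SAP.** That is true of the missing-data method. The scoring visit, however, is fixed by the Protocol itself, so this is a stated rule and not a gap.

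**The rule keeps everyone in the analysis, and later response is of interest.** Research question 3 does concern 6 and 12 months. But a mixture of visits answers neither the 1-month nor the 12-month question, and imputation also keeps every randomised participant.

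**Drop-out may be balanced.** With identical response in both arms and equal drop-out the artefact is zero. Nothing in the Protocol predicts imbalance. The lack of a fixed time point remains either way.

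Three stronger readings are tempting but not supported:

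- *That 6 points conflicts with the plan's own 10.* The 10 points come from the passage "where a clinically significant difference in treatment effects is 10 points, which is the between groups difference we aim to detect": a difference between arm means. The 6 points are a change within one participant, and the two can coexist. With "With a standard deviation of the CAPS-5 to be 20" and an assumed baseline–follow-up correlation of 0.5, the SD of change is 20 × √(2 × 0.5) = 20. Mean improvements of 5 and 15 then give response of 48% v 67% at 6 points and 40% v 60% at 10 points. The contrast is about 19 to 20 points at either threshold, so the lower one does not dilute it.
- *That a large 1-month difference would be lost through carrying forward.* Suppose response is 65% v 50% at 1 month and 65% v 65% at 12 months, with 80% of each arm last seen at 12 months, 10% at 1 month and 10% at baseline. The rule gives 0.8 × 65% + 0.1 × 65% = 58.5% v 0.8 × 65% + 0.1 × 50% = 57.0%. Of the fall from 15 points to 1.5, 13.5 come from assuming that control catches up fully by 12 months. Against the 12-month truth of zero, the rule errs by only 1.5.
- *That controls will receive later care that raises their scores.* The 1-MONTH FOLLOW UP section says only "The assessment will include the need for further psychiatric care". It does not say that care is given, or given differently by arm.

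**Conclusion.** The point holds for the time of scoring only. As written, response is a last-observation-carried-forward measure with no fixed visit. For everyone seen after 1 month it departs from the primary endpoint, and it can show a difference between arms that reflects when people left. In the illustrations the artefact runs from −6 to +4 points. It is zero when drop-out is equal and true response is the same in both arms. These sizes rest on assumed response rates and drop-out splits, and on leavers responding like stayers; the Protocol supplies none of these.

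The primary mixed-model analysis is untouched. This is therefore a change that should be made, not one on which the main conclusion depends. No contradiction between the 6-point and 10-point figures is claimed.

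**What to change.** Reword the definition so that response is judged at the fixed 1-month visit, and report the same definition separately at 6 and 12 months as secondary. Replace carrying forward with a missing-data method consistent with the mixed model, for example multiple imputation of the CAPS-5-CA score at each visit before response is derived. This also settles how participants with only a baseline score are treated. The 6-point threshold should not be moved to 10 on the strength of the between-group figure.

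The cost is a change of wording in the Protocol (and in the SAP, if one exists) and one additional imputation analysis. No new data or visits are needed.

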## PRIMARY MEASURES

Feasibility will be assessed by evaluating the study procedures and provision of the treatment using the RE-AIM framework, focusing on the intervention's reach (percentage eligible/excluded, reasons for refusal or exclusion), effectiveness (symptom reduction and impact on quality of life), adoption (attrition, adherence, client satisfaction), implementation (clinician resources), and maintenance (effects on symptom measures and measures of quality of life at the 6-month follow-up).

Treatment acceptability will be defined in accordance to the definition by Sekhon et al. (2017): "the extent to which people delivering or receiving a healthcare intervention consider it to be appropriate, based on anticipated or experienced cognitive and emotional responses to the intervention". This definition considers acceptability to consist of seven component constructs: affective attitude, burden, perceived effectiveness, ethicality,

intervention coherence, opportunity costs, and self-efficacy. We consider the proportion of participants that go through the entire treatment period, adverse events related to the treatment, number of dropouts and number of individuals offered the intervention but declined part of treatment acceptability. Qualitative interviews will be conducted and scheduled separately post-treatment with a focus on acceptability. Client Satisfaction Questionnaire (CSQ-8) will be used to assess patient satisfaction with treatment . Data on adverse events will be collected each treatment week using a standardized checklist (Safety Monitoring Uniform Report Form).

The primary outcome measure will be CAPS-5-CA, the gold standard clinical interview for PTSD that assess PTSD symptom severity and past month diagnosis of PTSD. CAPS-5-CA assesses the 20 DSM-5 PTSD symptoms, the onset and duration of symptoms, subjective distress, impact of symptoms on social and occupational functioning, improvement in symptoms since a previous CAPS administration, overall response validity, overall PTSD severity, and specifications for the dissociative subtype of PTSD (depersonalization and derealization).

Secondary outcome measures are self-rated PTSD symptom severity, other mental health problems, clinician-rated symptom improvement, global functioning, health-related quality of life, cost data, therapeutic alliance, treatment credibility, client satisfaction, adverse events.

## ASSESSMENT POINTS

The primary outcome measure, CAPS-5 CA, will be conducted at baseline, 1-month post-treatment (primary endpoint), and at 6-month and 12-month follow-ups (secondary endpoints). Self-administered measures will be used at baseline, post-treatment, 1-month post-treatment (primary endpoint), and at 6-month and 12-month follow-ups. Self-administered measures of PTSD (CATS-2) and adverse events are also administered weekly through the treatment period.

## OUTCOME MEASURES

- Clinician Administered PTSD Scale Children and Adolescent version 5 (CAPS-5-CA), the gold standard clinical interview to assess PTSD symptom severity and diagnosis of PTSD [42] at baseline and the 1-month, 6-months and 12-months follow up.
- The Child and Adolescent Trauma Screen (CATS-2) at baseline, weekly through the treatment period, post-treatment and at the 1-month, 6-month and 12-month follow up.
- Mood and Feelings Questionnaire (MFQ) at baseline, post-treatment and at the 1-month, 6-month and 12-month follow up.

- The Education, Work and Social Adjustment Scale, Youth and Parent (EWSAS) at baseline, post-treatment and at the 1-month, 6-month and 12-month follow up.
- Treatment Inventory of Costs in Psychiatric Patients (TIC-P) at baseline, post-treatment and at the 1-month, 6-month and 12-month follow up.
- The Negative Effects Questionnaire (NEQ) at post-treatment and at the 1-month, 6-month and 12-month follow up.
- Assessment of Quality of Life KIDSCREEN at baseline, post-treatment and at the 1-month, 6-month and 12-month follow up.
- The Client Satisfaction Questionnaire (CSQ-8) at post-treatment.
- The Working Alliance Inventory (WAI) after completion of treatment module 3.
- The Credibility/Expectancy Questionnaire (CEQ) after completion of treatment module 1.

## ASSESSMENTS AND PROCEDURES

### INCLUSION PROCEDURE

Participants will be recruited through the designated website for the study. Information about the study will be made available at psychiatric clinics and advertisements in social media and newspapers about the study. All participants will during the study period be patients at BUP Internetenhet or Save the Children.

In the first stage of recruitment to the study, interested applicants do an Internet-administered screening on an encrypted webpage using questions about inclusion and exclusion criteria, demographics, symptoms of post-traumatic stress, depressive symptoms, quality of life and alcohol and drug consumption. Written information about the study will be given before the screening including objectives, benefits, risks and requirements imposed by the study. The applicant is also provided with contact information to the study personnel and have the possibility to call and ask for more details or clarifications before signing informed consent in the digital platform.

Interested applicants are screened on the telephone, and preliminary eligible youths and their families are invited to a psychiatric assessment via video-conferencing or face-to-face. The aim of this visit is ensuring eligibility by verification that PTSD is the primary diagnosis and other inclusion/exclusion criteria, assess severity of PTSD symptoms, and assess for comorbidity. The gold standard clinical interview CAPS-5-CA that assesses past month diagnosis of PTSD and PTSD symptom severity will be used to ensure validity and reliability of the PTSD diagnosis. The interview will also include the child version of the Mini International Neuropsychiatric Interview version 7 (MINI-KID). According to clinical routines, a suicide-risk assessment is also mandatory.

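### Provider is neither balanced by the unrestricted allocation nor a term in the stated models; adding it is a low-cost, modest gain in precision if provider is fixed before allocation

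*Protocol*

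**What the plan says.** Three places in the Protocol bear on this.

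- **Inclusion procedure** names two providers: "All participants will during the study period be patients at BUP Internetenhet or Save the Children".
- **Description of the study** sets the allocation: two arms "on a 1:1 ratio without restriction", run by an external party after the decision to include. This wording rules out strata and blocks.
- **Sample size / Outcome measures** sets the primary analysis: a "linear mixed-effects model with fixed effects of time and group, their interaction, as well as random intercept and slope". The self-rated secondary outcomes get the same terms. Provider appears in neither model.

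Two further statements affect the size of the issue. Under Assessment points, "The primary outcome measure, CAPS-5 CA, will be conducted at baseline, 1-month post-treatment (primary endpoint), and at 6-month and 12-month follow-ups", so baseline is one of the outcome time points. The power paragraph says that "a clinically significant difference in treatment effects is 10 points" and takes a standard deviation of 20, then plans on d = 0.4.

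The Protocol does not say how participants divide between the providers, when a participant is assigned to one, whether each provider delivers both arms, or whether therapists differ between them.

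**The concern.** Provider is a structural feature of this trial. Two organisations may differ in the patients they reach and in the therapists who support them, although the Protocol does not say that they do. If recovery differs by provider, variation between providers becomes noise in the treatment comparison. Under unrestricted allocation the two arms can also end up with different provider mixes by chance.

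What is at stake is limited: some precision, and how the result is read if a visible imbalance turns up. Without a prespecified provider term, an imbalance seen after the fact invites a choice between adjusted and unadjusted results once both are known.

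**Working it through.** **Inputs from the Protocol.** SD 20; planning effect d = 0.4, which is 0.4 × 20 = 8 points; alpha 0.04, taken as two-sided because sidedness is not stated; total N given as 140 under Primary objective and 240 in the power paragraph. Both totals are carried through. The Protocol has no figure of its own on provider to reproduce.

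**Assumptions.** Share q of participants at one provider: 0.5, with 0.8 and 0.9 as less even splits. Provider difference g in CAPS-5 change: 2, 5 and 10 points. Provider is fixed before allocation. Attrition is ignored. The calculation uses a single-time-point linear model with total SD 20 as a stand-in for the mixed model.

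**Why g is a difference in change.** Baseline CAPS-5-CA is a model time point and the effect is carried by group by time. A constant severity gap between providers is present at baseline and at 1 month alike, so it largely cancels. Only a difference in change feeds through.

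**Step 1: chance imbalance in provider share between arms.** Its SD is 2·√(q(1−q)/N).
- N=140, q=0.5: 2·√(0.25/140) = 0.085; 95% of trials within ±1.96 × 0.0845 = ±16.6 percentage points.
- N=240, q=0.5: 2·√(0.25/240) = 0.065; within ±12.7 percentage points.

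**Step 2: shift in the realised estimate.** Shift = imbalance × g. The standard error of the unadjusted estimate is 2 × 20/√N, which is 3.38 at N=140 and 2.58 at N=240.

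| g (points) | 95% shift, N=140 | 95% shift, N=240 |
|---|---|---|
| 2 | ±0.33 | ±0.25 |
| 5 | ±0.83 | ±0.63 |
| 10 | ±1.66 | ±1.27 |

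Less even splits give less. At N=140 and g=10 the shift is ±1.33 for q=0.8 and ±0.99 for q=0.9.

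**Step 3: precision gained by adjusting.** The share of variance removed is q(1−q)g²/20². At q=0.5:
- g=5: 0.25 × 25/400 = 1.6%. Standard error 3.38 to 3.35 (N=140), 2.58 to 2.56 (N=240).
- g=10: 0.25 × 100/400 = 6.25%. Standard error 3.38 to 3.27 (N=140), 2.58 to 2.50 (N=240).
- g=2: 0.25 × 4/400 = 0.25%, which is no visible change.

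These figures leave out the price of estimating one more coefficient under unrestricted allocation, roughly 1/N of the variance (1/140 = 0.7%). That price exceeds the gain at g=2 and is covered at g=5 and above.

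**Step 4: simulation** (20,000 trials per scenario, q=0.5, true effect 8 points, two-sided alpha 0.04; the price above is included).

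| | Power without provider | Power with provider |
|---|---|---|
| N=140, g=5 | 61.5% | 61.8% |
| N=140, g=10 | 61.4% | 63.7% |
| N=240, g=5 | 85.0% | 85.2% |
| N=240, g=10 | 84.9% | 86.9% |

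The mean error of the estimate was within 0.05 points. Type I error was 3.8% to 4.3% with and without the provider term, against a nominal 4%.

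**The case against.** The strongest reply is that nothing invalid has been specified. Simple randomisation leaves the estimate unbiased, the standard error already includes chance imbalance, and the same could be said of any baseline variable left out of a model. Covariates are also often settled in a statistical analysis plan, which is not available here. And the Protocol describes much that is common to all participants: one study website, one screening and interview procedure, one digital programme and blinded assessors.

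Most of this stands. A reader might infer that provider imbalance biases the treatment effect, or passes straight into it. The documents do not support that: the shift is conditional on one realised allocation, is zero on average, and needs a provider difference in change. A reader might also take a 10-point provider difference as expected. It equals the whole target difference, nothing in the Protocol supports it, and it serves here only as the top of a range. Nor does the Protocol state that provider is known before randomisation. If provider were assigned afterwards, it could not be a stratum, and adjusting for it would not be a clean baseline adjustment.

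Two parts of the reply do not fully answer the point. Allocation is fixed in the Protocol, and a later plan cannot stratify retrospectively. The model terms are also written out rather than deferred, so a plan could add provider, but it would be extending a stated model. Provider differs from an arbitrary covariate in that it is part of how the trial is organised.

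**Conclusion.** The point holds as a low-severity, nearly free improvement. Provider is neither balanced nor adjusted for, yet neither bias nor an inflated type I error follows. Under a 50:50 split, the 95% chance shift is at most about half a standard error even at the top of the assumed range (1.66/3.38 = 0.49 at N=140; 1.27/2.58 = 0.49 at N=240), and much less for differences of 2 to 5 points. The power gain at N=140 is about 0.3 points for a 5-point difference and 2.3 points for a 10-point difference, with essentially none at 2 points.

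These sizes rest on an assumed split, an assumed provider difference in change, a single-time-point approximation, and provider being fixed before allocation. The Protocol gives none of these.

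**What to change.** 1. State in the Protocol that provider is assigned and recorded before randomisation, and that both arms are delivered at each provider.
2. Prespecify provider and provider by time as fixed effects in the primary CAPS-5-CA model and in the secondary mixed models. Provider by time is the term that matters, because a constant provider difference already largely cancels.
3. Optionally, if randomisation has not started, have the external randomisation party stratify by provider with concealed, randomly varying block sizes.

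**Cost.** Items 1 and 2 need a few lines of text and a two-level factor with its time interaction. The statistical price is about 0.7% of the variance at N=140 if providers turn out not to differ. Item 3 is a set-up change with a slight risk of predictable allocation, which central allocation and undisclosed block sizes limit. Item 2 is worth making even if allocation stays unrestricted, provided item 1 holds.
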